#### Self-Guided Yoga Practice

In addition to participating in the live, virtual classes, participants will also be given a self-guided yoga prescription to assist in the development of their personal practice. To facilitate self-guided practice, participants will be instructed to use video recordings from the study website, which will offer classes from the study’s Iyengar teachers of varying durations (eg, 15, 30, 45, and 60 minutes). The first 3 months will focus more heavily on live yoga instruction, and the last 6 months will be designed to foster a more autonomous practice. The self-guided prescription is based upon total duration (ie, minutes per week) rather than frequency (ie, days per week) to facilitate greater retention and adherence by allowing individuals the choice to practice yoga less frequently for a longer duration (eg, 1 time per week for 60 minutes) or more frequently for shorter durations (eg, 3 times per week; one, 30-minute class and two, 15-minute classes). Progression toward a total dose (ie, combination of live classes and self-guided practice) of 180 minutes per week of yoga practice is the intervention target for both the first 3 months and the final 6 months of the program.

#### Verbal Cues for Life Application (Yamas or Niyamas)

Asanas (ie, the physical practice of yoga poses) taught within classes will be infused with verbal teachings of yamas or niyamas (ie, social disciplines to guide relationships with oneself and others) to help cue participants into how yogic philosophies can overflow into everyday life (ie, how to apply skills practiced within class to personal experiences or struggles encountered outside of class). To ensure translatability of the yoga intervention, verbal cues will not explicitly discuss application to WL but will be broad enough so that participants can apply these principles to their weight control practices. Table 1 describes the 5 yamas and 5 niyamas, which simultaneously target several of the self-regulatory mechanisms examined within this study (eg, distress tolerance, mindfulness, and self-compassion). It is also important to note that many weight control behaviors can relate to several yamas and niyamas at once. For instance, choosing to eat and drink in moderation (vs overeating) so that one has more energy to engage in activities that one values can involve brahmacharya (moderation), aparigraha (nongreed), and satya (truth).

**Table 1. T1:** Yamas and niyamas used in yoga.

Practice		Description
Yamas		
	Ahimsa	Nonviolence; making sure not to harm oneself or others; not thinking negative thoughts; kindness and consideration.
	Satya	Truthfulness; being truthful in one’s thoughts, feelings, speech, and actions; being honest with oneself and others.
	Asteya	Nonstealing; not coveting; not being jealous; letting go of cravings. The need to “steal” often arises from a lack of faith in oneself.
	Brahmacharya	Moderation and channeling emotions; having moderation in our actions; conserving energy (slowing down); showing restraint.
	Aparigrapha	Nongreed; nonpossessiveness; greedlessness; simplicity; fulfilling needs rather than wants.
Niyamas		
	Saucha	Purification; cleanliness, internally and externally; purifying the body, mind, and surroundings.
	Santosha	Contentment; detaching from desires to cultivate inner peace.
	Tapas	Self-discipline; using self-discipline to burn out impurities of mind and body.
	Syadhyaha	Self-reflection; the practice of introspection; self-study.
	Ishvara Prandihana	Surrender; surrendering to a higher power.

#### Additional Yoga-Related Website Components

Instructions on how to properly and safely perform each yoga pose will be available on the study website, along with prerecorded videos for self-guided practice. To assist individuals with making the connection between weight control practices and what they are learning “on the yoga mat,” a brief statement applying a yama or niyama to a WL behavior will be added to the text messages that are sent out twice per month as a part of the IDWL program. Participants will self-monitor their yoga practice and log the daily number of yoga practice minutes on the study website.

#### Recommended Yoga Practice Following the 9-Month Yoga Program

The yoga prescription is designed to facilitate an autonomous practice, which could be continued after the intervention. Upon completion of the 9-month yoga intervention, participants will be encouraged to continue their personal yoga practice of at least 180 minutes per week with the tools taught to them during the intervention. Although no intervention will be provided during months 13‐18, participants will have continued access to the prerecorded videos, and participants will be asked to complete monthly surveys reporting on their yoga practice.

### Contact Control: Health and Wellness Program

Upon completion of the 3-month assessment visit, participants randomized to WELLNESS will receive a 9-month fully remote, health and wellness program. Similar to YOGA, wellness classes will be approximately 60 minutes in duration and held multiple times per week. Participants will be instructed to attend 2 classes per week for the first 14 weeks and 1 class per week until the 12-month study assessment (22 weeks). Classes will be taught by individuals with a bachelor’s degree or higher in a wellness-related field (eg, nutrition, exercise science, health promotion, and psychology). Classes will consist of lectures, handouts, videos, and discussions addressing a variety of health and lifestyle topics, which include immune health, sleep recommendations, health screenings, healthy aging, vitamins and minerals, and humor and health. WL will not be discussed within these sessions, and participants will be informed that wellness classes are designed to function independently of the IDWL program. Overall, the WELLNESS condition provides a treatment program, which serves as a contact-matched control for the yoga arm.

### Fidelity

All live intervention sessions (YOGA and WELLNESS) will be audio-recorded using a HIPAA-compliant version of Zoom. Recordings will be downloaded weekly and stored on a secure server. On a quarterly basis, 15% of all completed class recordings will be assessed for treatment fidelity via checklists developed by the research team for the YOGA and WELLNESS classes. These checklists include items such as class duration, whether the instructor taught the class as intended, and whether there was an opportunity for participants to ask questions. Fidelity will be assessed by a member of the research team who does not interact with participants. If at any time fidelity is <80%, teachers will be retrained and instructed on how to implement any necessary changes.

### Outcome Measures

#### Overview

Assessments of weight, aerobic exercise minutes, dietary lapses, potential lapse triggers, and self-regulation mediator variables will be measured at baseline, 3 months (just prior to randomization), 6 months (mid-treatment), 12 months (postintervention), and 18 months (following a 6-month period of no intervention). Both questionnaires and EMA will be used. Research staff members will not be blinded to group assignment, and efforts will be made to collect data from all enrolled participants at the time of each assessment, including those who may no longer be attending intervention classes. Brief descriptions of study measures are provided below.

#### Anthropometric Measures

Weight change throughout the intervention period will be objectively assessed using Wi-Fi and Bluetooth-enabled smart scales (Withings Body), which will be mailed to study participants upon enrollment. At each assessment period, participants will be instructed to weigh first thing in the morning before eating or drinking, without clothing, or in light clothing. They will be asked to weigh 3 consecutive times, and if the maximum difference between any 2 weight measurements is ≤0.5 kg, the mean of the 3 weights will be used in the analysis. If the difference between any 2 weights is >0.5 kg, the weight that is farthest from the median will be dropped, and the mean of the remaining 2 weights will be used. Height will be self-reported, which has high concordance with stadiometer-assessed height measurements [58].

#### Ecological Momentary Assessment

##### Overview

Participants will complete brief surveys for 10 days at each assessment period. All entries will be made in response to 5 semirandom prompts delivered throughout the day via text message. Upon receiving a text message with a one-time link to the survey, participants will have 45 minutes to answer the questions. Each survey begins with the following message: “When completing this survey, please read the questions carefully as some may ask about how you feel ‘right now,’ others may ask what you may have experienced ‘since the last survey,’ and some questions may allow you to ‘select all response options that apply’ versus just one option. Please be as honest and accurate as possible. Your genuine input will help us gain valuable insights into your daily experiences.” Each survey will take 2‐5 minutes to complete.

##### Dietary Lapses and Potential Lapse Triggers

At each survey, participants will be asked if they ate since the last EMA prompt. If eating was endorsed, a series of questions related to dietary lapse will be asked in addition to questions about potential triggers for lapses. These questions are included in Table 2. When eating is not reported, participants will receive a set of supplemental questions, which do not directly address study aims, to maintain consistency in survey structure and reduce response bias. This approach is consistent with previous work studying dietary lapse [39].

**Table 2. T2:** Summary of ecological momentary assessment variables to be collected.

Variable	Measure	Response options
Dietary lapse		
Dietary lapse (type or total)^a^	Since your last survey (even if it was yesterday), at how many meals or snacks did any of the following occur? (a) Ate past the point of feeling full. (b) Ate a bigger portion than you meant to. (c) Had unplanned eating (ie, ate or drank when you do not usually eat or drink and were not making up for a missed meal). (d) Ate a food that you were intending to avoid or reduce. (e) Went over a calorie goal that you had in mind for yourself.	Number of lapse events
Dietary lapse (frequency)^b^	On the previous question, you indicated that since the last prompt, at least one of the following occurred at XX meals or snacks since the last survey (number from above question will be piped in). Now we want to know at how many meals or snacks did each of the following occur: (1) Ate past the point of feeling full. (2) Ate a bigger portion than you meant to. (3) Had unplanned eating (ie, ate or drank when you do not usually eat or drink and were not making up for a missed meal). (4) Ate a food that you were intending to avoid or reduce. (5) Went over a calorie goal that you had in mind for yourself.	Number of each type of lapse
Potential dietary lapse triggers		
Dietary temptation (type)^c^	Since the last survey (even if it was yesterday), have you experienced any of the following temptations to eat or drink, regardless of whether or not you actually acted on the temptation (check all that apply)?	(a) I was tempted to overeat, (b) I had a sudden urge to eat a tempting food or drink that I have been trying to reduce or avoid, (c) I was exposed to a tempting food or drink, (d) none of the above
Dietary temptation (details)^d^	If a, b, or c are selected from the question above, the following questions will be asked: (1) thinking about the most recent temptation you had: what was the intensity of the temptation? (2) Did you eat or drink the tempting food or drink?	(1) 1‐7 Likert scale; 1=not at all intense, 7=extremely intense; (2) yes or no
Craving	How strong is your craving to eat a specific food right now?	Visual analog scale: 1=low intensity to 10=high intensity
Momentary affective experience (or related interoceptive state indicators)	(1) Right now, I feel calm, tense, upset, relaxed, content, worried, hungry, stressed, tired, bored, anxious, overwhelmed, ashamed, energetic; and (2) Right now, I feel very good, good, fairly good, neutral, fairly bad, bad, very bad	(1) 5 Likert scale; 1=not at all, 5=extremely; (2) −5 to 5 Likert scale; −5=very bad, +5=very good

a This will be the question used to calculate the total number of lapses.

b This will be the question used to determine the frequency of endorsed types of lapses, if applicable.

c This question will be used to assess the type of dietary temptations.

d These questions will be used to assess the intensity of and ability to resist dietary temptations.

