#### Secondary Aims

Using a similar analytic approach as that described for the primary aim, we will examine intervention effects on secondary outcomes, including frequency of dietary lapses and potential lapse triggers (eg, affect, cravings, and ability to resist dietary temptations), as assessed via EMA. Namely, longitudinal mixed effects models will be specified that regress outcomes over time on intervention group (YOGA vs WELLNESS), time, intervention*time, baseline value of the outcome, and confounders. Models will also adjust for the clustering of data within participants. Effects of day and measurement period will be tested, and adjustments made, as needed.

To evaluate the secondary aims of this study, we will examine potential mediators (eg, affect, mindfulness, self-compassion, and distress tolerance) of the treatment effect on primary (ie, weight change) and secondary outcomes (ie, dietary lapses) using a multiple mediator model with bootstrapped SEs (10,000 bootstrapped samples). Models estimate the path coefficients (a path: effects of YOGA vs WELLNESS on changes from baseline in potential mediators and b path: effects of changes from baseline in potential mediators on WL or lapse outcomes) as well as the indirect effect of intervention (ab path: YOGA vs WELLNESS on outcomes through the mediators).

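### The eating gate and the lapse count use different recall windows, and the interval a count covers varies with missed prompts, so unequal EMA compliance could bias the lapse comparison in either direction

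*Protocol article*

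**What the plan says.** In the protocol article, section Dietary Lapses and Potential Lapse Triggers, the survey opens with a filter: "At each survey, participants will be asked if they ate since the last EMA prompt". The consequence of a yes is: "If eating was endorsed, a series of questions related to dietary lapse will be asked in addition to questions about potential triggers for lapses". After a no, the participant gets supplemental questions that do not address the study aims.

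In Table 2 the count item reads: "Since your last survey (even if it was yesterday), at how many meals or snacks did any of the following occur". Its footnote states: "This will be the question used to calculate the total number of lapses". The follow-up item on types of lapse uses both windows in one sentence: "you indicated that since the last prompt, at least one of the following occurred at XX meals or snacks since the last survey".

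The Ecological Momentary Assessment overview gives five prompts a day for 10 days, each open for 45 minutes. The Secondary Aims analysis section says that the models will "regress outcomes over time on intervention group (YOGA vs WELLNESS), time, intervention*time, baseline value of the outcome, and confounders". It adds adjustment for clustering within participants and, where needed, for day and measurement period. Compliance below 80% excludes a person at baseline. At 3, 6, 12 and 18 months there is payment per survey and a bonus for compliance above 80%.

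**The concern.** The last prompt and the last completed survey are the same moment only if no prompt has been missed. Two separate problems follow.

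1. **Unasked intervals.** A gate that looks back one prompt controls access to an item that looks back to the last completed survey. Someone who missed prompts, lapsed in that stretch and has not eaten since the most recent prompt is routed away from the lapse items. The next survey starts a new window, so those lapses are never recorded.
2. **Variable exposure.** When the lapse item is shown, its count covers one interval plus every missed interval before it. The listed model terms contain nothing for this length.

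Lapse frequency is a secondary outcome and also an outcome in the mediation analysis. If compliance at follow-up differs between YOGA and WELLNESS, part of the arm contrast in lapses could reflect survey-answering behaviour.

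**Working it through.** **The article's own figure.** 5 prompts per day × 10 days = 50 surveys per assessment, as stated under Ethical Considerations. The payment also agrees: 25 + 0.50 × 50 + 25 = US $75.

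**Assumptions (the article gives no figures for these).** Equal-length prompt intervals, eating in each interval with probability q, and the same true lapse rate λ per interval in both arms. Lapses occur only in intervals with eating. Prompts are answered at random with probability c. The mean number of missed intervals before an answered prompt is then about (1 − c)/c.

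**Step 1: lapses lost under the gate as written.** Lapses in a missed interval are recorded only if the next answered survey passes the gate, which has probability q. The share lost is about (1 − c)(1 − q).

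| Compliance c | q = 0.6 | q = 0.8 |
|---|---|---|
| 80% | 0.2 × 0.4 = 8% | 0.2 × 0.2 = 4% |
| 60% | 0.4 × 0.4 = 16% | 0.4 × 0.2 = 8% |

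**Step 2: mean count per completed survey, gate as written.** This is λ[1 + q(1 − c)/c]. With q = 0.75:
- c = 0.80: 1 + 0.75 × 0.250 = 1.188
- c = 0.70: 1 + 0.75 × 0.429 = 1.321
- c = 0.65: 1 + 0.75 × 0.538 = 1.404

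Ratios with one arm at 80%: 1.188/1.321 = 0.90 against 70%, and 1.188/1.404 = 0.85 against 65%. The less compliant arm looks worse.

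**Step 3: 10-day sum, gate as written.** The recorded share is 1 − (1 − c)(1 − q). With q = 0.75 it is 0.950, 0.925 and 0.9125 at 80%, 70% and 65%. Ratios: 0.950/0.925 = 1.03 and 0.950/0.9125 = 1.04. The less compliant arm now looks better.

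**Step 4: 10-day sum, both windows running from the last completed survey.** Missed intervals are caught up by the next survey. Only those after the final answered prompt are lost, about (1 − c)/c of 50 intervals: 0.25/50 = 0.5% at 80% and 0.54/50 = 1.1% at 65%. The ratio is about 0.995/0.989 = 1.01, so there is almost no bias.

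**Step 5: would an offset cure it?**
- *Plain offset for the whole window, gate as written:* the rate is still reduced by the lost share, so the ratios are again about 1.03 and 1.04.
- *Gate-aware exposure:* after a no-eating answer, only the last interval counts. Per survey, expected lapses are λ + qλ(1 − c)/c and expected exposure is 1 + q(1 − c)/c. Their quotient is λ at any compliance, so the ratio is 1.00.

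A simulation with 50 prompts and 40,000 participants per setting agreed with these formulas at q = 0.75: 0.90 and 0.85 per survey, 1.03 and 1.05 for the sum, 1.03 and 1.04 with the plain offset, and 1.00 with gate-aware exposure.

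**The case against.** The strongest reply is that this is a condensed article. The unit of analysis, link function and any offset commonly sit in an analysis plan that is not shown, and the references to confounders and to day effects leave some room. That is a fair limit: the article does not show that exposure will be ignored, only that the terms it lists do not include it. It does not answer the window mismatch, because an analysis plan cannot recover lapses the survey never asked about.

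A second reply is that the gate wording is the article's description, not quoted item text, and that prompt and survey may simply be used as synonyms. The participant preamble in the EMA overview does refer to the last survey. This may well be right, which is why the first step is to check the live instrument.

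A third is that nothing in the article suggests unequal compliance, and the incentives are the same in both arms. This stands. A reader might infer that the trial will show a spurious reduction in lapses for YOGA. The documents do not support that. It would need lower compliance in WELLNESS and an analysis per completed survey, and neither is stated. The footnote's reference to a total allows a sum, for which the sign reverses or the bias nearly vanishes.

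**Conclusion.** The mismatch is on the page, and it occurs even within a single Table 2 item. Followed literally, it loses about 4-8% of lapses at 80% compliance and 8-16% at 60%, for eating in 60-80% of intervals.

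Bias in the arm comparison is possible, not established. It requires a compliance difference at follow-up, for which the article gives no figure, and its size and sign depend on an aggregation rule that the article does not state. For 80% versus 70% or 65% compliance and eating in 75% of intervals, the false ratio is about 0.90 or 0.85 per completed survey and about 1.03 or 1.04 for a 10-day sum. A sum with both windows running from the last completed survey is nearly unbiased. All of this assumes prompts missed at random and equal intervals.

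The point concerns the secondary lapse outcome and the mediation analysis that uses it. It does not touch the primary weight outcome. It should be settled before lapse data are compared by arm.

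**What to change.** 1. Confirm which window the live survey uses, and make the gate and both Table 2 lapse items agree.
2. Analyse lapses as a rate, with a log link and an offset for the log of the prompt intervals, or waking time, covered since the last completed survey. Clock hours are a poor choice because the first window of each day includes sleep.
3. If the live gate runs from the last prompt, count only the interval since that prompt as exposure when the answer is no eating. A plain offset leaves the ratio at about 1.03-1.04 in the example above.
4. Report EMA compliance by arm and visit.

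The cost is a slightly more complex model and some programming with existing survey timestamps. The offset needs no change to the survey. With four of five cohorts already launched, data already collected under a prompt-window gate cannot regain the unasked lapses, but step 3 keeps the rate comparison valid under the stated assumptions.

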We recently published findings from our pilot RCT (n=60), wherein 60 female individuals with overweight and obesity were randomized to a 3-month yoga program or a contact-matched control (cooking or nutrition classes) following 3 months of behavioral WL treatment [4,51]. Adherence (attendance to the yoga classes was 75%) and retention (100%) were high. Yoga participants reported fewer lapses from the recommended diet (eg, via less overeating, stress eating, and loss of control when eating) and less difficulty resisting dietary temptations compared to the control group. Post-hoc analyses revealed that yoga was associated with a larger magnitude of 6-month WL and several self-regulatory skills (mindfulness, distress tolerance, and self-compassion) compared to the control, among those who lost more weight in the first 3 months of treatment (≥5%). These results led to the hypothesis that yoga can not only decrease the likelihood of dietary lapse but also reduce many common factors, which could potentially trigger a dietary lapse contributing to longer-term WL success. Additionally, in this pilot trial, we found online delivery of a yoga program to be feasible. Specifically, due to COVID-19, one cohort in this study received yoga classes remotely (live via videoconferencing), and attendance and satisfaction ratings were comparable to in-person yoga classes administered in the previous cohort. These preliminary findings demonstrate initial feasibility and acceptability of including yoga within the context of a WL program and indicate that yoga can reduce dietary lapses and improve self-regulation, 2 factors important for long-term weight control.

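### Resistance and temptation intensity are scored only in surveys that report a temptation, so the planned arm comparison on ability to resist is not protected by randomisation

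*Protocol article*

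**What the plan says.** All references are to the protocol article.

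- **The gate.** Under Dietary Lapses and Potential Lapse Triggers, Table 2 first asks which kinds of temptation occurred. The list of options ends "c) I was exposed to a tempting food or drink, (d) none of the above". The follow-up on intensity and on whether the food was eaten comes only after a positive answer: "If a, b, or c are selected from the question above, the following questions will be asked". It concerns the most recent temptation.
- **The scales.** The responses are "1=not at all intense, 7=extremely intense; (2) yes or no". The lowest intensity anchor still describes a temptation that was reported, so the scale has no value for no temptation.
- **What the items measure.** Footnote d: "These questions will be used to assess the intensity of and ability to resist dietary temptations". Footnote c assigns the preceding item to the type of temptation.
- **The comparison.** The analysis section on Secondary Aims compares arms on "potential lapse triggers (eg, affect, cravings, and ability to resist dietary temptations), as assessed via EMA". The models "regress outcomes over time on intervention group (YOGA vs WELLNESS), time, intervention*time, baseline value of the outcome, and confounders". The article describes no term for whether a temptation occurred.
- **The hypothesis.** The Introduction expects yoga to "reduce many common factors, which could potentially trigger a dietary lapse". Both the Introduction and the Study Overview list dietary temptations among the potential triggers.

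**The concern.** Whether a temptation is reported in a follow-up survey is an event after randomisation, and the trial's own hypothesis gives a reason to expect yoga to change it. The resistance and intensity items exist only where that event occurred. If the arms differ in which temptations still arise, the model compares two differently selected sets of surveys. A difference in the resisted share may then reflect the mix of temptations left and not any change in resisting. Randomisation balances the participants but does not balance these subsets of surveys.

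At stake is the interpretation of one named secondary outcome and of the intensity measure that accompanies it. The primary weight outcome and the lapse count are not affected by this gate.

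**Working it through.** **No figure to reproduce.** The article gives no temptation frequency and no resistance rate. The only design input is 5 prompts × 10 days = 50 surveys per assessment. Everything else below is an assumption, chosen to show direction.

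**Assumed WELLNESS participant.** 50 answered surveys, all carrying the temptation item, with at most one scored temptation each:
- 10 weak temptations, 80% resisted, intensity 3
- 10 strong temptations, 30% resisted, intensity 6

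**Formulas.**
- Conditional resistance = resisted temptations / surveys with a temptation
- Conditional intensity = sum of intensities / surveys with a temptation
- Yielded-to rate = temptations yielded to / 50

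**WELLNESS.**
- Resistance: (10 × 0.8 + 10 × 0.3) / 20 = 11/20 = 55.0%
- Intensity: (30 + 60) / 20 = 4.5
- Yielded to: 9/50 = 0.18

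**YOGA.** Resistance to each kind of temptation is unchanged, and five temptations are removed:

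| Removed | Conditional resistance | Conditional intensity | Yielded to, per survey |
|---|---|---|---|
| 5 weak | (4 + 3)/15 = 46.7% | (15 + 60)/15 = 5.0 | 8/50 = 0.16 |
| 5 strong | (8 + 1.5)/15 = 63.3% | (30 + 30)/15 = 4.0 | 5.5/50 = 0.11 |
| 2.5 of each | (6 + 2.25)/15 = 55.0% | (22.5 + 45)/15 = 4.5 | 6.75/50 = 0.135 |

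Fewer temptations are yielded to in every row. Conditional resistance falls, rises or stays put, although no resistance probability changed.

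**Sensitivity to the assumed rates (5 weak removed).** With weak/strong resistance of 90/10%, the share goes from 50.0% to 36.7%. With 60/40%, it goes from 50.0% to 46.7%. With 50/50%, it does not move. The effect needs both a difference in how resistible temptations are and an uneven removal.

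**Illustrative simulation.** Assumptions:
- 84 analysed per arm (210 × 0.8 / 2)
- on average 5 strong and 5 weak temptations per window, with a between-person coefficient of variation of 0.6 in the rates
- yielding 50% for strong and 10% for weak, with a person-level SD of 0.6 on the logit scale
- a t test on each person's resisted share

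| Weak temptations removed | Change in resisted share, points (shared / independent person-level rates) | Significantly worse for YOGA (shared / independent) |
|---|---|---|
| 25% | -2.8 / -2.5 | 11% / 11% |
| 50% | -6.5 / -5.5 | 43% / 33% |
| 75% | -11.7 / -10.4 | 85% / 78% |

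Random removal gave no bias. Removing half of the strong temptations gave +5.7 points with independent rates, again with no change in resistance.

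**Participants with no score.** Under the same assumptions about 0.3% (independent) to 1.4% (shared) of WELLNESS participants report no temptation in a window. With 75% of weak temptations removed this becomes about 2% to 4%. The problem is therefore mostly the mix of scored surveys within people, not the loss of whole participants.

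**The case against.** **The analysis plan may settle the scoring.** The article fixes the items but does not spell out the estimator, and it allows zero-inflated distributions. A plan that is not shown may define a score for surveys without a temptation. That is a fair limit. What the article does fix is the gate, footnote d and the comparison of arms on ability to resist. The approaches under Missing Data do not resolve this: resistance without a temptation is undefined, not unobserved.

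**Resistance is conditional by nature.** Resisting presupposes a temptation, and an outcome that treats not being tempted and having resisted alike is not ability to resist. This stands. It is why the conditional measure should be kept and the new outcome added beside it.

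**Much of the information is already there.** Temptation occurrence is recorded, and yielding to an avoided food overlaps with one of the lapse types. This also stands. It makes the improvement cheap and limits the damage.

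**A reader might infer that the plan will make YOGA look worse at resisting.** The documents do not support that. Nothing says that weak temptations go first, and removal of strong ones would flatter YOGA. The article reports that pilot yoga participants had less difficulty resisting temptations. It hypothesises a reduction in lapse triggers generally and does not separately predict fewer temptations. One option, exposure to a tempting food, is largely environmental.

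**The simulation is not the planned analysis.** It uses an unadjusted t test, whereas the plan has a longitudinal mixed model with the baseline value and Hommel adjustment. Its percentages are not error rates for this trial.

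**Conclusion.** The point holds as a limit on interpretation with an inexpensive remedy. Resistance and intensity are defined only within surveys selected by a post-randomisation event that yoga may change, so their difference between arms cannot be read as a randomised effect on resisting.

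Neither direction nor size can be settled from the documents. With five of 20 assumed temptations removed, the resisted share ranged from 46.7% to 63.3% against 55.0%, with true resistance held constant. It did not move under proportional removal. These figures rest wholly on assumed rates and on an assumed weak/strong contrast.

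Two stronger readings are not supported: that the sign will be reversed against YOGA, and that many participants drop out of the comparison.

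**What to change.** 1. Keep resistance and intensity given a temptation, and state that they describe tempted surveys and are not randomised treatment effects.
2. Add an arm comparison over all answered surveys that carry the temptation item: 1 if a temptation was reported and yielded to, 0 if none was reported or it was resisted.
3. Show temptation occurrence by arm beside it, together with conditional resistance.
4. Analyse intensity with a two-part model (occurrence, then intensity given occurrence). A 0 placed on a 1 to 7 scale would be arbitrary.

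**Cost.** Wording in the analysis plan only, with no new data. Enrolment is described as ongoing, so it can be set before analysis. The downside is that the added outcome mixes fewer temptations with better resistance, which is why its parts must be shown with it.

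**What it does not solve.** As the article reads, trigger questions are asked only when eating was endorsed. The added comparison stays within those surveys. That is a separate issue.
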